### Statistics

We will analyze the pooled data from the three timely different editions with a 10-month intervention each. Data clean-up will be performed to minimize errors. To compare groups, we will use the Student-t test for continuous variables and chi-square test for categorical variables. Allocation to the intervention group will be performed at the CCC level (clusters) by convenience. Therefore, generalized estimating equation (GEE) models will be fitted to assess intervention effect on BMI z-score and other secondary outcomes at individual level. To assess the outcome at family level, we will apply mixed models.

Due to the small number of clusters, GEE models estimation will be followed by t test with the Kauermann and Carrol-corrected sandwich estimator. In alternative, we will use the Wald t test with the FG-corrected sandwich estimator, depending on the variation in cluster size (function saws from R package saws) [50]. FG-corrected sandwich estimation is not possible with mixed models. For this reason, we will apply GEE models for the analyses. BMI z-score and other secondary outcomes at baseline will be used as covariates to adjust the models. Final models will be adjusted for baseline covariates such as: age, sex, mothers educational level, adherence to the Mediterranean diet, PA, and the corresponding anthropometric variable (function mgee from R-packagesaws). A fidelity score will also be included as a covariate in the models. Differences between the intervention and control group were considered significant if *p*<0.05. All analyses will be carried out using SPSS V21.0 and R.

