### Subjects

The study will involve low SES children aged 812years and their families from 60 Community Child Centers (CCC) in the metropolitan area of Barcelona. A CCC is a childcare center that promotes the education of children from low income families by providing them academic support and emotional education after school. A total of 810 children and 600 parents will be included in the intervention groups, and likewise for the control groups. These population samples will be distributed among three consecutive editions of the FIVALIN project (20192020, 20202021, and 20212022), and will include at least one adult and one child per low-income family. A total of 30 CCC (15 in the intervention group and 15 as controls) will be involved per edition. CCC from control group will be invited to be part of intervention group on the subsequent edition, and15 new CCC will be recruited in the control groups of the second and third editions. In total, after the three edition, 60 CCC will be enrolled in the project (see Table1). It is not expected that CCC participating in the intervention group during first or second edition will continue providing the intervention in subsequent editions. 18 socioeconomic vulnerable children (8- to 12-year-old) and their families will participate per CCC. Therefore, considering the intervention and control groups, we expect a total participation of 540 children and 400 adults per edition. Participants will be recruited by CCC, by inviting families that are already participating in their activities. They receive communicative material (flyers and leaflets) to introduce the project and motivate them to participate. For convenience, recruitment and allocation will be conducted by Gasol Foundation (GF), considering the characteristics of the CCC: activities, number of educators, parents involvement, etc.

**Table 1 Tab1:** Number of CCC per FIVALIN edition

CCC from the	1st edition	2nd edition	3rd edition
Intervention group	1 to 15 CCC *(new)*	CCC from the control group of the 1 edition 16 to 30 CCC	CCC from the control group of the 2 edition 31 to 45 CCC
Control group	16 to 30 CCC *(new)*	31 to 45 CCC *(new)*	46 to 60 CCC *(new)*

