##### Other data collected

Additional data will be collected about the following items:
Socioeconomic status (annual income, and educational and occupational levels)Smoking statusFamily meals per weekFamily PA per weekFamily postal addressNumber of years parents and children have been living in SpainHousehold characteristicsC.**Data collection for educators and CCC**

We will collect data on CCC characteristics, such as: (i) location; (ii) total number and ages of children, and family workshop and sport educational sessions attendance; (iii) number of people of the staff; and (iv) if applicable, number and characteristics of health promotion actions implemented in the CCC. The latter will be collected at the beginning of the project. Moreover, we will also collect CCC staff data on the following parameters: (i) socio demographic characteristics; (ii) educational level and studies; and (iii) grade of motivation and awareness through healthy lifestyle promotion, at the beginning and at the end of each edition.

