Finally, the potential bias based on non-randomized CCC group intervention assignment would be also a limitation because, the CCC and educators could have a higher level of motivation to participate in the high intensity modality. As highlighted, this could influence project effectiveness. Data regarding CCC and staff characteristics will be collected and are described in methods section.

In conclusion, the FIVALIN project will contribute to prevent childhood obesity among socioeconomically vulnerable families. It will do so by using a multiple behavioral approach to simultaneously target healthy eating, PA, screen time, sleep quality and duration, and psychological wellbeing. Moreover, the behaviors targeted are considered to be at the same level of importance and will be analyzed as both primary and secondary outcomes. This approach will provide evidence on the influence of each behavioral area on the evolution of the weight status [29].

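### Centres are allocated by convenience with centre characteristics in view, but no centre-level baseline covariate is named for the final models

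*Protocol article*

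**What the plan says.** On assignment, the Statistics section states: "Allocation to the intervention group will be performed at the CCC level (clusters) by convenience". Under Subjects, recruitment and allocation are carried out by the coordinating foundation, "considering the characteristics of the CCC: activities, number of educators, parents involvement, etc".

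On the model, the Statistics section fits GEE models with a small-sample corrected sandwich estimator to the pooled data of three editions. It states: "BMI z-score and other secondary outcomes at baseline will be used as covariates to adjust the models". It continues: "Final models will be adjusted for baseline covariates such as: age, sex, mothers educational level, adherence to the Mediterranean diet, PA", and closes that list with the corresponding anthropometric variable. It then adds: "A fidelity score will also be included as a covariate in the models".

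On centre data, the part of Other data collected that covers educators and CCC begins: "We will collect data on CCC characteristics, such as: (i) location; (ii) total number and ages of children". It goes on to attendance, number of staff and "if applicable, number and characteristics of health promotion actions implemented in the CCC", the last recorded at the beginning of the project. Staff motivation and awareness are recorded at the beginning and end of each edition.

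On the bias, the Discussion names non-randomised assignment of centres as a limitation and answers: "Data regarding CCC and staff characteristics will be collected and are described in methods section". It gives these data no use in the analysis.

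**The concern.** In a non-randomised cluster comparison, the covariates that matter most are those that influenced which cluster went to which arm and that may also relate to the outcome. Here the document says what was considered at allocation, and all of it belongs to the centre. The named adjustment set works at another level. Child age, sex, mother's education, diet, physical activity and baseline zBMI can differ little between arms while staffing or existing health-promotion work differs a good deal.

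The corrected sandwich estimator does not help with this. It repairs standard errors for clustering and few clusters, and leaves the point estimate where confounding put it. If centres better placed to change went more often to one arm, part of that advantage would be read as an intervention effect, or would hide one.

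**Working it through.** **1. Allocation factors against the model.** No figure in the plan quantifies this point, so the first step is a comparison of sections.

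| Factor | Source | Collected? | Named in the model? |
|---|---|---|---|
| Centre activities | Subjects | Partly: health-promotion actions, at project start | No |
| Number of educators | Subjects | Number of staff; timing not stated | No |
| Parents' involvement | Subjects | Not listed as a baseline centre measure | No |
| Educator motivation | Discussion | Yes, at start and end of each edition | No |

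Workshop and session attendance is also listed among the centre data, but it arises after allocation. So does the fidelity score, whose level (child, family or centre) is not stated.

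**2. Pooled imbalance under Table 1.** Inputs: the intervention arm is centres 1–15, 16–30 and 31–45; the control arm is centres 16–30, 31–45 and 46–60; each centre contributes 18 children per edition. Let pA, pB and pC be the share of centres with a stable trait among centres 1–15, 16–45 and 46–60.

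- Intervention: (15·pA + 30·pB)/45
- Control: (30·pB + 15·pC)/45
- Difference: 15·(pA − pC)/45 = (pA − pC)/3

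The 30 shared centres cancel. The largest possible difference, with pA = 1 and pC = 0, is 1/3, or 33 percentage points. With pA = 0.8 and pC = 0.2 it is 0.6/3 = 0.20.

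**3. Bias from leaving the trait out.** Bias = imbalance × effect of the trait on zBMI change. The document gives no trait effect, so a range is assumed. The percentages are of the 0.15 target in the sample size section.

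| Assumed trait effect (zBMI) | 80% v 20% split (imbalance 0.20) | Ceiling (imbalance 1/3) |
|---|---|---|
| 0.02 | 0.004 (3%) | 0.007 (4%) |
| 0.05 | 0.010 (7%) | 0.017 (11%) |
| 0.10 | 0.020 (13%) | 0.033 (22%) |

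**4. Check by simulation, on assumed values.** The setting was no true effect, 60 centres in the Table 1 pattern, 14 children per centre and edition (18 × 0.8 = 14.4), an assumed ICC of 0.02, and 2,000 runs. The outcome SD was 0.556. The plan states no SD, so this one is back-solved from 270 per group with 20% loss: 0.15 × √(216/2) / (1.960 + 0.842) = 0.556. The trait was continuous. D is its difference, in SD, between centres 1–15 and 46–60, and the trait effect is per SD.

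- Trait effect 0.05, D = 0.5: the formula gives 0.05 × 0.5/3 = 0.008; the simulated bias was 0.010 in size, with type I error 5.9%.
- Trait effect 0.10, D = 1.0: the formula gives 0.10 × 1.0/3 = 0.033; the simulated bias was 0.032 in size, with type I error 13.8%.
- With the centre covariate in the model, the bias was about 0 and type I error about 4–6%.

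**The case against.** The strongest reply is that the covariate list is open, that this is a journal article, and that a complete list may stand in an analysis plan that is not shown. A reader might infer that centre variables are excluded from the model. The text does not support that; it supports only that none is named. What remains is that the article does describe its final models, and every baseline example it gives is at a different level from its own allocation factors.

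A second reply is that the design limits the damage. This stands. Thirty of the 45 centres in each pooled arm are the same centres, each edition has 15 concurrent control centres, and baseline zBMI is adjusted for. A reader might picture the pooled arms differing 80% v 20% on a trait, which at 0.10 would give 0.6 × 0.10 = 0.06, or 40% of the target. Table 1 rules that out for a stable trait, unless invited control centres decline or the trait changes between editions. Nor is it right to say that pooling does nothing or that adjustment is the only protection. These features shrink the bias without removing it, because centres 1–15 and 46–60 each appear in one arm only and the GEE as described does not condition on centre.

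A third reply is that confounding is not shown. This stands in part. The Discussion speaks of potential bias, and illustrates it by motivation to join the high-intensity modality, a choice made within the intervention arm. Its remarks on educator motivation and parental involvement concern how well an intervention works, which is effect modification. Considering centre characteristics at allocation might even have served to balance the arms. So known confounding would be too strong a term. The reported similarity of the first edition's groups does not settle the matter either, since it covers socio-demographic characteristics in one edition only.

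**Conclusion.** The point holds as a gap between the stated allocation process and the named adjustment set. The factors considered in assigning centres belong to the centre, the document acknowledges potential bias, relevant data are collected, and no centre-level baseline variable is named in the model. The fidelity score is no substitute.

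The direction and actual size of any bias are unknown. For one stable trait with an assumed effect of 0.10 zBMI, the bias in the pooled analysis cannot exceed about 0.033, and it is smaller for less extreme splits or weaker traits. These figures assume that Table 1 is carried out as planned, with equal centre sizes and a trait that does not change between editions. Several traits acting in the same direction would add up. The result is a moderate threat to the estimate that is cheap to reduce.

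**What to change.** In the Statistics section, name a short pre-specified set of baseline centre covariates for the final GEE models: number of staff, health-promotion actions at project start, and staff motivation at the start of the edition. State when number of staff is recorded, since the article gives no timing for it. Report the balance of these variables by arm at centre level, and show the intervention effect with and without them.

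Include parents' involvement only if what was considered at allocation was recorded. The article describes no rating of it, so one should not be assumed to exist.

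The cost is analysis wording for data already planned, and a few cluster-level degrees of freedom out of about 60 centres. The plan already corrects for a small number of clusters, so the set should stay at about three variables.

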**Family (children and adults)**			
**8 family workshops** (2h/workshop) involving a group of 15 to 20 children and parents from each CCC implemented in the CCC by GF staff with the support of CCC educators.	Yes. 8 Workshops: (1) Baseline evaluation (2) Welcoming (3) Sleep duration and quality (4) Healthy Diet (5) Emotional Wellbeing (6) PA & Sport (7) Closing (8) Final evaluation		Yes. 3 Workshops: (1) Baseline evaluative (2) General health awareness (3) Final evaluation
**32 mobile messaging** sent to participants families by using text, images, and infographics methods: (1) 8 mobiles messages, 1 before each family workshop, to recall families and promote their attendance. (2) 8 mobile messages, 1 after each family workshop, to reinforce the health topics promoted in the workshops. (3) 16 mobile messages, 1 after each cycle of 2 sport educational sessions dedicated to each healthy habit to reinforce it.	Yes	Yes	No
**8 challenges videos** done by high profile supporters (such as professional athletes and celebrities) posing a healthy challenge as a family related to one health topic.	Yes	Yes	No
**Health promotion educational material** shared with families after each workshop to reinforce the health messages shared in the sessions and workshops.	Yes	Yes	Yes

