### Evaluation plan

We will collect all data for each edition at baseline and 10months after the intervention (post-evaluation). Moreover, a follow up evaluation will be performed in the intervention group 12months after the post-evaluation, to study whether the impact of FIVALIN is sustained in the long term. After the assessment sessions, each participating family from the intervention and control groups will receive an incentive (e.g., a reusable water bottle, a technical shirt, or a ball).

The intervention fidelity and process evaluation indicators will be assessed in different ways, such as: i) periodical project coordinators meetings; ii) follow-up meetings and evaluation sessions with CCC educators; iii) voice audios after project activities recorded by GF educators; iv) registration of family attendance and level of satisfaction after each workshop; and v) a qualitative assessment at the end of each project edition (focus groups and interviews to key stakeholders). The evidence derived from the previous assessment activities will be used with 2 aims, such as: (i) improve the project management after each edition; and (ii) incorporate future improvements to the project basis, once the three editions will be implemented and the final data of the present study will be gathered. The project methodology, activities, assessment tools, staff profile, and the expected outcome will be the same for the 3 editions because a final evaluation of pooled data will be performed.

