One limitation of the FIVALIN project could be the self-selection biases. Considering that participation is voluntary, parents with concerns about their childrens weight or health behavior might be more interested in the study. Moreover, CCC educators individual awareness and motivation could influence the effects of the intervention. The project also poses the challenge of how to engage parents. Parents involvement has to be considered as a potential agent of change in the development of their childrens health-related behaviors [14]. A systematic review indicated that the level of parental involvement appeared to positively impact the effectiveness of interventions on childrens weight and energy balance-related behaviours [53]. Another compilation report suggests that interventions promoting participant engagement may be more beneficial to disadvantaged groups than to higher literacy/SES status families [54]. Various parental characteristics are associated with low participation: low SES, single parenthood, difficult living circumstances, stress, family dysfunction, and belonging to a minority group ethnicity [55]. Therefore, it is important to take these risk factors into account in order to improve the efficacy of preventive actions [15]. We will undertake several strategies to minimize the effects of the above-mentioned barriers as described in the methods section. The reliance on self-report over objectively measured is a weakness commonly assumed by the intervention studies. Another limitation is not having a complete fidelity assessment to analyze project adherence and competence beyond family attendance and few actions related to process assessment. Although the fidelity plan must be improved, we have prioritized the definition and implementation of a feasible assessment plan to not produce an overburden to families and CCC educators. Thus, in the FIVALIN project, we take the opportunity to implement assessment methodologies as voice message, that could contribute to future intervention addressed to families experimenting vulnerability, to establish a feasible strategy to monitor fidelity.

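### The models for the intervention effect adjust for a fidelity score measured after allocation, so the arm coefficient need not be the total effect of FIVALIN

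*Protocol article*

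**What the plan says.** The Statistics section gives the purpose of the models: "generalized estimating equation (GEE) models will be fitted to assess intervention effect on BMI z-score and other secondary outcomes at individual level". It then lists the adjustment set: "Final models will be adjusted for baseline covariates such as: age, sex, mothers educational level, adherence to the Mediterranean diet, PA", together with the corresponding anthropometric variable. All of these are baseline measures. The next sentence adds one that is not: "A fidelity score will also be included as a covariate in the models". No effect model without the score is named, and no dose-response or per-protocol purpose is given for it.

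The Evaluation plan lists the sources of fidelity and process data. They include "registration of family attendance and level of satisfaction after each workshop" and "follow-up meetings and evaluation sessions with CCC educators", as well as voice reports and qualitative work at the end of each edition. It gives this evidence two uses: managing the project between editions and improving it later. The Discussion names as a limitation "not having a complete fidelity assessment to analyze project adherence and competence beyond family attendance and few actions related to process assessment".

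Table 2 gives intervention families 8 workshops. The control entry reads "Yes. 3 Workshops: (1) Baseline evaluative (2) General health awareness (3) Final evaluation". Mobile messages, challenge videos, educator training and follow-up meetings are for the intervention arm only. The 32 sport sessions are for the high-intensity modality only.

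**The concern.** The trial asks what FIVALIN does to BMI z-score compared with control. Attendance and delivery occur after a centre has been allocated and are part of how the programme is meant to act. With such a variable in the model, the arm coefficient compares children at the same fidelity value. That is a different question, and part of the effect may be moved into the fidelity coefficient.

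There is a second problem. The Discussion links low participation to low SES, single parenthood, stress and family dysfunction, and says that parental involvement influences how well such interventions work. Attendance therefore also carries family characteristics. If the same score value means different things in the two arms, conditioning on it compares unlike families, in a design that is already not randomised.

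The rule covers the primary BMI z-score contrast and the other outcomes analysed by GEE.

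**Working it through.** **1. Timing and role.** Every covariate in the named list is baseline. Every fidelity source in the Evaluation plan arises during or after delivery. The score is thus the only post-allocation term.

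**2. The algebra.** In a linear model the adjusted and unadjusted arm coefficients satisfy

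adjusted = unadjusted - b x D,

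where b is the within-arm slope of the outcome on the score and D is the difference in mean score between arms. The two agree only if b or D is zero.

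Example: suppose the whole effect is proportional to workshops attended, intervention families attend 5.3 of 8 on average (about two thirds), and controls are scored 0. Then b = -0.15/5.3 = -0.0283 per workshop and D = 5.3. The adjusted effect is -0.15 - (-0.0283 x 5.3) = 0.

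**3. Inputs for a simulation.**
- From the article: effect 0.15; 15 centres per arm per edition and 3 editions, so 15 x 3 = 45 centre-editions per arm; 18 children per centre and 20% loss, so 18 x 0.8 = 14.4, taken as 14; 8 and 3 workshops.
- SD: not stated. It was solved from the article's 270 per arm per edition: 270 x 0.8 = 216 evaluable, and n = 2(1.960 + 0.842)^2 SD^2/0.15^2 = 216 gives SD of about 0.556. The 270 is therefore attainable but cannot be verified (SD 0.5 would give 219 and SD 1.0 would give 873).
- Assumed: ICC 0.02; mean attendance about two thirds, driven by a latent family engagement with the same distribution in both arms.
- Method: linear model with cluster-robust standard errors, 600 data sets per scenario.

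**4. Without the score.** The mean estimate was between -0.147 and -0.157 in every scenario, SE 0.035, power 0.98 to 1.00.

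**5. With the score.** The engagement link means a BMI z-score lower by 0.1 per SD of engagement, in both arms.

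| Scoring (correlation with arm) | Attendance unrelated to outcome | Whole effect through attendance | Engagement link only | Both |
|---|---|---|---|---|
| Workshops attended (0.77) | -0.149 | -0.079 | -0.002 | +0.073 |
| Controls set to 0 (0.91) | -0.152 | -0.005 | +0.074 | +0.213 |
| Share of own arm's workshops, equal attendance rates (0.00) | -0.150 | -0.157 | -0.151 | -0.155 |

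The SE is 0.051 to 0.052 in the first row, 0.075 to 0.076 in the second and 0.035 in the third. When attendance is unrelated to outcome there is no bias, but power falls from 0.99 to 0.82 (first row) or 0.52 (second row). When the whole effect runs through attendance it falls to 0.33 or 0.04.

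**6. A variant of the share.** Table 2 counts the baseline and final evaluations as workshops. If measurements are taken there, a child with both measurements has attended at least 2 of 3 in control but only 2 of 8 in intervention. With engagement still equal between arms, the mean share was 0.74 in intervention and 0.88 in control (correlation with arm -0.38). The adjusted estimate was -0.15 if attendance is unrelated to outcome, -0.17 if the effect runs through attendance, and -0.19 to -0.22 with the engagement link. Here the effect is exaggerated.

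**The case against.** The article does not define the score: not its components, scaling, level or value for controls. A condensed article may leave that to a fuller plan, so the missing definition is not itself an error. Several stronger readings are therefore not supported.

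- A reader might infer that the score is fixed by arm or does not exist for controls. Controls have three workshops, Table 2 marks voice reports after workshops for them too, and attendance registration is not limited to one arm. Nothing says that controls are scored 0, so that row shows only what such a choice would do.
- A reader might infer that the bias is towards no effect. The results above include a null, a reversal, an exaggeration and no change.
- The score need not be a workshop count. The Discussion mentions some process measures besides attendance, and all the scenarios are attendance-based.
- The power of about 0.99 without the score is not the trial's power. Table 1 has centres 16 to 45 serving first as control and then as intervention, so there are 60 distinct centres. The simulation does not model that overlap.

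All of this stands and limits what can be said about size. It does not remove the main point. However the score is built, the plan puts a post-allocation variable into the effect models and names none without it. Nor does the lack of randomisation justify it: that calls for adjustment for characteristics that precede allocation, and attendance during the programme is not one.

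**Conclusion.** The rule is wrong as written for estimating the total effect of FIVALIN. That rests on the text alone: the purpose of the models, the timing of the fidelity data, and the absence of an effect model without the score.

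That the score is related to arm is a reasonable inference from the unequal offer in Table 2, but it depends on the scoring. The consequence for the estimate is therefore uncertain in direction and size. For a true effect of -0.15, the illustrative range is about -0.22 to +0.21, including values close to -0.15. It rests on the assumed SD, ICC, attendance and engagement link. The documents do not support a claim that the effect will be removed. They do show that the primary estimate would hang on a scoring choice that the article does not state.

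**What to change.** In the Statistics section, delete the sentence that adds the fidelity score to the models. State instead that the models for the intervention effect on BMI z-score and all other outcomes adjust for baseline covariates only. If fidelity is to be analysed, describe it as a separately labelled secondary or exploratory analysis, for example dose-response within the intervention arm, with the score defined there and the result not read as the programme effect.

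Keeping a fidelity-adjusted model as a clearly secondary analysis, beside a named main model without the score, would also protect the main estimate. The cost is one or two sentences; no data collection changes.
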